## Abstract

**Background:**

Digitalization and electronic health (eHealth) offer new treatment approaches for patients with migraine. Current smartphone applications (apps) for migraine patients include a wide spectrum of functions ranging from digital headache diaries to app-based headache treatment by, among others, analysis of the possible triggers, behavioral therapy approaches and prophylactic non-drug treatment methods with relaxation therapy or endurance sport. Additional possibilities arise through the use of modern, location-independent communication methods, such as online consultations. However, there is currently insufficient evidence regarding the benefits and/or risks of these electronic tools for patients. To date, only few randomized controlled trials have assessed eHealth applications.

**Methods:**

SMARTGEM is a randomized controlled trial assessing whether the provision of a new digital integrated form of care consisting of the migraine app M-sense in combination with a communication platform (with online consultations and medically moderated patient forum) leads to a reduction in headache frequency in migraine patients, improving quality of life, reducing medical costs and work absenteeism (DRKS-ID: DRKS00016328).

**Discussion:**

SMARTGEM constitutes a new integrated approach for migraine treatment, which aims to offer an effective, location-independent, time-saving and cost-saving treatment. The design of the study is an example of how to gather high quality evidence in eHealth. Results are expected to provide insightful information on the efficacy of the use of electronic health technology in improving the quality of life in patients suffering from migraine and reducing resource consumption.

## Introduction

Migraine is a primary headache disorder affecting ~15% of people worldwide (1). The Global Burden of Disease 2015 study lists migraine as the number one source of disability caused by a neurological disease (2). Migraines can disrupt patients' daily life and diminish their quality of life. Moreover, migraine is the first cause of disability in patients under 50 and often leads to an incapacity to work in these productive years (3).

Nevertheless, patients suffering from migraine face numerous barriers to effective migraine care, including not being able to consult a specialist, failure to receive a correct diagnosis, and not being prescribed a regimen with acute and preventive pharmacologic treatments (4). Multidisciplinary treatment approaches have been shown to be an efficient therapeutic option in headache disorders (5). Patients with migraine benefit from cognitive behavioral interventions (6, 7), but waiting lists for psychotherapy appointments in Germany are long and access is further restricted in rural areas.

Self-management programmes have shown to be effective for long-term conditions (8). In the case of headaches, such programmes can help patients take an active role in the management of their disease, by learning more about the condition and through behavioral changes (9). Several non-pharmaceutical behavioral interventions such as relaxation therapy and endurance sports are important for migraine management but need instruction and patients' motivation (10). Moreover, the recurring nature of this condition often leads to the frequent intake of medication, which itself may further increase headache frequency, known as medication overuse headache (11). Education in non-pharmacological prevention is thus key to prevent chronification and medication overuse (12).

Digital healthcare tools can help, at least partially, to address the aforementioned challenges.

The interest in smartphone applications (“apps”) that are used for diagnostics or treatment of medical conditions has been increasing in various medical fields (13, 14). While there are many smartphone applications for headache disorders, high-quality studies that evaluate their efficacy and possible benefit (or harm) are still lacking. A review on mobile apps for the management of headache disorders by Mosadeghi-Nik et al. found a low level of clinical evidence for (at this time) existing smartphone applications that included a diary function and intervention elements (15). However, authors and reviewers considered smartphone applications to have a high potential for the improvement of care for headache patients (16–18). Further communication tools such as expert chats and patients' forums offer easy access to information and counseling and may also be effective in migraine treatment.

The purpose of SMARTGEM (smartphone assisted migraine therapy) is to assess with a randomized controlled trial if the provision of digital tools in migraine therapy may lead to a reduction of migraine frequency, improve quality of life, reduce medical costs and prevent work absenteeism in patients with migraine. SMARTGEM is a new digital integrated form of care that consists of the medically certified migraine app M-sense in combination with a communication platform (with online consultations and a medically moderated patient forum).

## Methods

### Hypothesis

The implementation of SMARTGEM, consisting of the certified medical app for migraine (M-sense) in combination with a communication platform (with online consultations and medically moderated patient forum), leads to a decrease in monthly migraine days in patients with migraine with at least 5 migraines days per month after 6 month.

### Intervention and Control

The SMARTGEM intervention consists of three elements:

#### M-Sense app

M-sense is a medically certified app that was developed independently of SMARTGEM and prior to the project start by an interdisciplinary team of scientists, psychologists, app developers and economists (Newsenselab GmbH) in cooperation with physicians.

Patients in the intervention group had access to all the functions of the M-sense app (called M-sense active). The app included a headache diary, where participants can fill in their headache attacks' characteristics. This comprises the start and endpoint of the headache attack, maximal pain intensity, whether the headache is unilateral, whether it is a throbbing headache, if an aura is present, as well as information on concomitant symptoms—aggravation due to physical activity, aura, vomiting, nausea, phonophobia, and photophobia. Furthermore, for each headache attack, patients may document the intake of acute medication, including the name and dose of the drug and time of intake. The smartphone can also add information on weather data (temperature, air pressure, etc.) to the diary.

The app classified each headache attack as migraine, tension-type headache (TTH), or non-migraine or non-TTH, using a standardized, validated algorithm (19) based on the International Classification of Headache Disorders (ICHD-3) criteria (20). A migraine day was defined as a calendar day on which the patient suffered from a qualified migraine attack. A headache day was defined as any calendar day on which the patient experienced a headache attack (including migraine).

To identify if an attack should be considered as a migraine or a TTH, all relevant ICHD-3 criteria were applied by the algorithm (19). A qualified migraine attack needed to fulfill the following ICHD-3 criteria (20) for being classified as migraine: a headache with or without aura lasting at least 4h with both features A (at least 2 of the following: unilateral location, pulsatile quality, moderate or severe pain intensity, and aggravation caused by physical activity or avoidance of physical activity) and B (during headache, at least 1 of the following: nausea and/or vomiting and/or photophobia and phonophobia). Headache attacks accompanied by the intake of migraine-specific medication (such as triptans) to treat a headache or accompanied by aura were considered as migraine, regardless of the duration and pain characteristics or concomitant symptoms.

In addition to the attacks' characteristics as well as their symptoms, patients could also document their sleep patterns, stress levels, skipped meals, coffee and/or alcohol consumption. The app version available to patients in the intervention group analyzed these factors with the aim of defining a possible connection with the patient's headache patterns, thus identifying individual triggers.

For patients in the intervention group, the app also offered preventive modules that enable the patient to take an active role in their migraine management (21). The therapy module offered different relaxation methods — such as progressive muscle relaxation according to Jacobson or autogenic training — as well as created individual training programmes for endurance sports. Another module offered animated physio-therapeutic exercises. Patients could access these according to a personalized plan, but in the case of acute headaches, they could also get help in an acute module via guided imagination exercises and physiotherapy exercises. In an educational module, patients could deepen their knowledge about migraine via a “chatbot” and learn basic behavioral therapy approaches in migraine therapy.

#### Patient's Forum and Experts' Chat

Patients had access to a secured web based communication platform with an individual login. Via this platform, they could consult the physicians of the participating headache centers using an expert chat. Each center provided several time slots per week for synchronous communication. Patients could also ask their questions outside these time slots and were provided with an answer during the next 24 h (asynchronous communication). A patients' forum moderated by the physicians of the participating headache centers was also provided.

However, SMARTGEM did not allow continuous medical support 24/7 in the current concept. In case of an emergency like refractory migraine attack, persisting aura or unusual headache symptoms all patients were instructed to introduce themselves immediately at the emergency department of the participating centers (which provide a neurologist on call 24/7) or another hospital nearby.

#### Telemedicine

Physicians of the participating headache centers had access to the digital headache diary of their patients. This enabled the physicians to online monitor the course of the migraine during treatment and could be used for online consultations.

Furthermore, resident doctors providing the ongoing treatment of patients (neurologists, pain specialists or general practitioners) could consult with headache experts of the headache centers and discuss treatment based on the digital headache diary.

### Study Overview

SMARTGEM is a multi-center, two-armed, open-label, randomized controlled trial comparing standard of care plus the use of a certified medical app for migraine (M-sense) in combination with a communication platform (with online consultations and medically moderated patient forum) vs. standard of care plus a basic version of M-sense app with a headache documentation function only. The study design was developed following the guidelines of the International Headache Society for controlled trials of prophylactic treatment in migraine (22). Figure 1 outlines the study flow and the timeline of SMARTGEM.

**Figure 1 F1:**
[figure not shown]
SMARTGEM's study flow.

### Recruitment and Study Participants

Adult patients (≥18 years old) previously diagnosed with migraine with less than three prior visits to the outpatient headache centers were recruited from the three participating sites (Charité — Universitätsmedizin Berlin, Universitätsmedizin Rostock and Universitätsklinikum Halle). Additionally, any adult patient who was scheduled for a first visit in the headache outpatient centers and was interested in participating could go through a telephone pre-screening. Successfully pre-screened patients got access to the basic functions of the M-sense app and were asked to fill in the app diary on a daily basis for 28 days previously to their first appointment with a headache specialist and clinical investigator (baseline). To be eligible for trial inclusion, patients had to have a migraine according to the ICHD-3 criteria (20) with at least five migraine days during the 28 day pre-baseline phase and a headache diary compliance of at least 80%. Further inclusion and exclusion criteria are described in the Supplementary Table A1. Only patients that gave their written informed consent were included in the study

After the pre-baseline phase, all patients that still met the inclusion criteria were randomly assigned to the intervention or the control group. Patients in the intervention group received standard care and all functions of SMARTGEM. Patients in the control group received standard care together with a basic version of M-sense app that serves only as an electronic headache diary.

SMARTGEM also included patients who were planned for participation in an existing multimodal treatment programme (KopfschmerzSPEZIAL) at the Charité — Universitätsmedizin Berlin. Patients in this programme were evaluated with regard to neurologic, psychological and physiotherapeutic aspects and a treatment plan was customized according to their needs. Furthermore, severely affected patients underwent a multi-modal, outpatient therapy programme, including, among others, group sessions and one-to-one discussions, guidance on endurance sports and individual physiotherapy training.

Potential participants were recruited over a 23 month period (January 2019 to December 2020). Participants were followed for 12 months.

### Study Objectives and Outcomes

A list of the primary and the secondary outcomes is presented in Table 1. All primary and secondary outcomes will be assessed at month 6 in comparison to baseline and between groups.

**Table 1 T1:** Study outcomes and data collection method.

**Outcomes**	**Data source**	**Timepoint**
*Primary Outcome* Migraine days per 28 days	M-sense electronic diary	Baseline vs. month 6
*Secondary outcomes*		
Responder rate (patients with ≥50% reduction from baseline in migraine days/month)	M-sense electronic diary	First six months in the study
Headache days per 28 days	M-sense electronic diary	Baseline vs. month 6
Days of acute medication intake	M-sense electronic diary	Baseline vs. month 6
HIT-6 score	Study databank	Baseline vs. month 6
EQ-5D-5L score	Study databank	Baseline vs. month 6
PROMIS 29 scores	Study databank	Baseline vs. month 6
Overall health care costs	Claims' data	Six months prior study initiation versus six months after study initiation
Days with inability to work	Claims' data	Six months prior study initiation versus six months after study initiation

*HIT-6, Headache Impact-Test 6; PROMIS 29, Patient-Reported Outcome-measurement Information System*.

The primary outcome is the reduction of migraine days per 28 days from baseline, as measured 6 months after inclusion in the study. Using data collected by M-sense, we will analyze the secondary endpoints regarding the number of patients with at least 50% reduction in migraine days per 28 days, the reduction of headache days per 28 days, as well as days of acute medication intake. Patient-related outcome measures will be assessed with validated surveys. In order to evaluate the impact of SMARTGEM on patients' quality of life we collect data with the Headache Impact-Test 6 (HIT-6) (23), Patient-Reported Outcome-measurement Information System 29 (PROMIS 29) (24) and German EQ-5D−5L (25). Furthermore, we will assess depression, anxiety and tension/stress of the patients with the depression anxiety stress scale (DASS) (26) and patients adherence with the Medication Adherence Report Scale (MARS-D) (27).

The aforementioned endpoints will also be analyzed at the follow-up periods (month 3, 6, 9 and 12), but in an explorative fashion only, i.e., without formally testing hypotheses by statistical tests. Additional exploratory endpoints are listed in the Supplementary Table A2.

Claims' data from the participating statutory health insurance will be collected to analyze participants' healthcare resources' consumption and work absenteeism.

Exploratory subgroup analyses for the primary and secondary outcomes will be carried out. This is intended to provide insights about which groups of patients particularly benefit from SMARTGEM with regard to their chronification stage:

Episodic migraine
○ Medium-frequency episodic migraine (between 5 and 7 migraine days per month and less than 15 headache days per month)○ High-frequency episodic migraine (at least 8 migraine days per month and less than 15 headache days per month)
Chronic migraine
○ Chronic migraine without medication overuse○ Chronic migraine with medication overuse

Chronic migraine was defined according to the ICHD-3 criteria (20). Medication overuse was defined as a) use of conventional analgesics (non-opioid analgesics such as non-steroidal anti-inflammatory drugs (NSAIDs) or paracetamol on at least 15 days/months or b) triptans on at least 10 days/months or c) combination therapy (any combination of triptans, ergotamines and analgesics) on at least 10 days per month. We used the definition from Tepper et al. (28). It should be noted that this definition should not be confused with the diagnosis of medication overuse headache. The subgroups were developed using patients' baseline data and the diagnosis of the physician according to the first study visit. Patients with chronic migraine had to have at least 15 headache days per month, of which at least 8 were migraine for >3 m before screening and assessed by the M-sense headache diary during the baseline period.

Physicians record data on patients' pharmacological and non-pharmacological therapies. Further study-specific questionnaires are used to obtain additional information as regards the satisfaction with the programme from the patients' and physicians' perspective.

We used the REDCap software to collect and record data (29).

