During the COVID-19 pandemic in-person outpatient health care visits plummeted (40). Thus, measures that allowed access to treatment and management of illnesses were essential. Due to the location-independent nature of SMARTGEM, patients could still benefit from the study. Those in the intervention group could manage their condition with behavioral modules offered in M-sense (relaxation exercises and endurance sports) even during the COVID-19 pandemic. Another study conducted in Italy during the pandemic showed promising results regarding the use of a behavioral approach offered in a smartphone app for the management of chronic migraine with medication overuse (41). Intervention-group patients in SMARTGEM could also continue to use the communication platform (with online consultations and a medically moderated patient forum) safely from their homes. In terms of the study flow, follow-up visits at month six were on site, while during other time points were by telephone. During the COVID-19 lockdown, we offered patients the possibility to do their 6-months visit per telephone, which was appreciated by some patients.

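### The Hypothesis and Study Objectives wording allows a before-after reading of the outcomes; for the diary outcomes that reading is invalid because the baseline window is also the entry filter (minor)

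*Protocol article*

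**What the plan says.** Study Objectives and Outcomes gives two comparisons for each outcome: "All primary and secondary outcomes will be assessed at month 6 in comparison to baseline and between groups". It defines the primary endpoint as a change: "The primary outcome is the reduction of migraine days per 28 days from baseline, as measured 6 months after inclusion in the study". In Table 1 the Timepoint column sets baseline against month 6 for most diary and questionnaire outcomes. For costs and days unable to work it reads "Six months prior study initiation versus six months after study initiation".

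The Hypothesis section says that SMARTGEM "leads to a decrease in monthly migraine days in patients with migraine with at least 5 migraines days per month after 6 month". It names no comparator.

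Recruitment and Study Participants requires "at least five migraine days during the 28 day pre-baseline phase". That diary runs for the 28 days up to the first specialist appointment, which the article labels baseline. No other diary window before randomisation is described, and the subgroup definitions refer to the same diary as the baseline period.

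Sample Size Calculation bases the sample size on migraine days at 6 months in the intervention group against the control group. Statistical Analysis puts treatment group in the primary model and compares secondary outcomes between groups. Adjustment for baseline covariates in the secondary analyses is left to be made where it proves necessary.

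**The concern.** A comparison with baseline is valid evidence of an effect only if the outcome would otherwise have stayed level. Here it would not. Patients enter because one 28-day count was high enough, and that same count is the baseline. Part of each qualifying count is month-to-month noise, so the average at month 6 will be lower whatever treatment is given. This is regression to the mean. It applies directly to migraine days and to the 50% responder rate, and by correlation to headache days and acute medication days.

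The Discussion adds a second source of decline: an observational study in which migraine frequency fell over time in regular users of the basic diary app.

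Costs and days unable to work use six-month claims windows, so the entry filter does not act on them in this way. Their weakness in a before-after comparison is calendar time. The Discussion notes that "During the COVID-19 pandemic in-person outpatient health care visits plummeted", and recruitment ran from January 2019 to December 2020.

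What is at stake is what may later be reported as efficacy. If a fall from baseline in the intervention arm could be presented as confirming the hypothesis, the claim would rest on a contrast that randomisation does not protect.

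**Working it through.** **The plan's own figures.** The article gives no figure for the expected before-after change, so none can be reproduced. The only planning number used here is the evaluable sample of 500, allocated 1:1, which gives 250 per arm. The enrolment target agrees with it: 500 / (1 − 0.13) = 574.7, that is 575, or 576 for equal arms, as stated. The 80% power cannot be checked because no effect size or SD is given, and nothing below depends on it.

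**Set-up of the no-effect simulation.** From the article: entry at 5 or more migraine days in 28 days, the same count used as baseline, and 250 patients per arm. Assumed, because the article does not give them:
- a stable patient-specific mean, gamma distributed, with population mean 6, 8 or 10 days and SD 3 or 4;
- two independent 28-day counts per patient around that mean, with variance 1 or 1.5 times the mean, capped at 28;
- no treatment effect and no time trend.

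This makes 12 scenarios, with a month-to-month correlation of 0.37 to 0.73 before selection.

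**Quantities.** Fall = mean baseline count − mean later count, among patients with baseline ≥ 5. Expected z for one arm = fall / (SD of change / √250).

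**Results.**
- Fall: 0.33 to 1.31 days.
- Expected z: 1.2 to 4.6. It exceeds 1.96 in all eight scenarios with mean 6 or 8 and in none of the four with mean 10.
- Share with a fall of at least 50% by chance: 9.9% to 26.2%. This is illustrative only, since Table 1 defines the responder rate over the first six months and not over a single month.

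**Check with a different noise model.** Within-patient noise was taken as normal with SD 2 or 3, the unselected mean as 5, 7 or 9, and the between-patient SD as 3 or 4. The correlation was about 0.5 to 0.8. Two examples:
- Mean 7, SDs 3 and 3: baseline 8.96, later 7.90, fall 1.06, SD of change 3.92. z = 1.06 / (3.92 / 15.81) = 4.3.
- Mean 9, SDs 3 and 2: baseline 9.63, later 9.38, fall 0.25, SD of change 2.77. z = 0.25 / (2.77 / 15.81) = 1.4.

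Over all 12 settings the fall was 0.25 to 1.62 days, and a one-arm pre-post test would reject with probability 0.30 to nearly 1.00.

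**The randomised comparison.** In four of these settings the change from baseline was compared between two arms of 250 with no true effect. The rejection rate was 0.050 to 0.053, which is the nominal 5%. The fall is expected equally in both arms and cancels.

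**Claims outcomes.** No arithmetic is possible. The article gives neither the size of the pandemic drop nor the number of patients whose before and after windows lie on different sides of it.

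**The case against.** The strongest reply is that no within-arm test is planned. Sample size, primary model and secondary tests are all between groups, and Statistical Analysis describes the intervention effect as relative to control. On this view the month-6 sentence means change from baseline, compared between groups. The Table 1 entries stand in a column of time points and name no tested contrast. The limitation about diary use in the Discussion also shows that the authors judge efficacy by the difference between arms.

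Most of this stands. It rules out the stronger readings that a reader might infer: that the trial's main result is biased, that a fall in the intervention arm alone would count as success under the plan, or that lockdown could produce the cost result. Regression to the mean and a concurrent fall in visits are expected in both randomised arms, and the specified tests compare those arms.

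It does not remove the inconsistency. The month-6 sentence joins the two comparisons with an and, the hypothesis names no comparator, and nothing labels within-arm change as descriptive. The statement that no hypotheses will be tested is attached to the explorative follow-up analyses. This suggests that the month-6 comparisons are the tested ones, although month 6 is also in that explorative list, so the boundary is unclear. The diary limitation is raised only as an obstacle to detecting a group difference; selection on the baseline value is not mentioned.

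**Conclusion.** The point holds in limited form and is minor. The Hypothesis section, the Study Objectives section and Table 1 permit a before-after reading that the sample size and analysis sections do not share, and selection on the baseline count makes that reading invalid for the diary outcomes. With no effect, the expected fall is about 0.3 to 1.3 days per 28 days. This size rests wholly on assumed means, SDs and month-to-month variation. It shrinks as the recruited population lies further above five days, and at an unselected mean of 10 days the expected fall would not reach significance with 250 patients in an arm.

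The randomised comparison is unaffected. The selection argument should not be extended to costs and days unable to work; there a before-after contrast is exposed to calendar-time change that the article does not allow anyone to size.

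**What to change.** 1. Hypothesis: state that the decrease in migraine days from baseline to month 6 is larger in the intervention group than in the control group.
2. Study Objectives and Outcomes, and Table 1: make the between-group difference at month 6 the only comparison used for testing and efficacy claims, in line with Sample Size Calculation and Statistical Analysis. Report within-arm changes descriptively, without p-values.
3. Costs and days unable to work: compare the six months after randomisation between arms, with the prior six months as a prespecified covariate in place of adjustment only where judged necessary.

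Items 1 and 2 are changes of wording. Item 3 uses claims data that are already to be collected and can add precision. No data and no power are lost for the randomised comparison.

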One strength of the study is that its design and its endpoints followed the recommendations of the guidelines for controlled trials in migraine (22). Although these guidelines were developed for the design of drug trials, we believe that the same strict criteria should be applied to digital or other non-pharmacological interventions whenever possible. Limitations of this study are possible bias resulting from the selection of particularly motivated patients and patients with an affinity for smartphone usage. Given answers may in part result from social expectations. One major limitation is that the type of digital intervention does not allow to blind patients to study groups which could increase bias. Claims' data from statutory health insurances in Germany are subject to delays of about 9 month, inherent in their updating since, especially outpatient data, are not promptly communicated. Hence, patients claims' data will only be evaluated within a 6 months period in order to guarantee their analysis within the project duration. A further limitation is that the regular use of a digital headache diary alone might lead to a decrease of headache frequency in migraine patients. This might be explained by a raise of awareness and identification of possible patterns and aggravating factors. This might impede the detection of differences between the control group and the intervention group.

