## Conclusion

SMARTGEM constitutes a new digital approach for migraine treatment, which aims to offer an effective, location-independent, time-saving and cost-saving treatment. Results are expected to provide insightful information on the efficacy of the use of electronic health technology to improve the quality of life of patients suffering from migraine and to reduce consumption of healthcare resources and loss of work productivity.

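### The tested cost endpoint is drawn from insurer claims alone, so it cannot support a cost-saving conclusion if any part of SMARTGEM's own cost is not billed to the insurer

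*Protocol article*

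**What the plan says.** Table 1 of the protocol article (Study Objectives and Outcomes) lists "Overall health care costs" among the secondary outcomes. Its data-source column gives claims data and nothing else, comparing six months before with six months after study initiation. The text below the table confirms the source: "Claims' data from the participating statutory health insurance will be collected to analyze participants' healthcare resources' consumption and work absenteeism". The Discussion fixes the window: "Hence, patients claims' data will only be evaluated within a 6 months period in order to guarantee their analysis within the project duration".

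The Statistical Analysis section compares secondary outcomes between groups by t-test or Brunner-Munzel test, with a Bonferroni adjustment. Cost is therefore formally tested.

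The aims are broad. The Introduction asks whether digital tools can "improve quality of life, reduce medical costs and prevent work absenteeism in patients with migraine". The Abstract describes an approach that "aims to offer an effective, location-independent, time-saving and cost-saving treatment", and the Conclusion repeats this.

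Study Overview defines the intervention arm as "standard of care plus the use of a certified medical app for migraine (M-sense) in combination with a communication platform", against standard care with a diary-only app. On the expert chat, the article states: "Each center provided several time slots per week for synchronous communication". Questions outside those slots are answered within 24 hours, and centre physicians moderate the forum. Under Telemedicine, they can also monitor diaries online and advise the treating doctors.

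**The concern.** A statement that a programme saves money has to count what the programme costs. The components above use a commercial developer's app, a platform and specialist physician time, and they fall on one arm. Under Randomization, control patients could receive the intervention only after six months, so the whole cost window contrasts an arm with these resources and an arm without them.

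Claims record what is billed to the insurer. The article nowhere says that the app, the platform or the physician time is billed. The limitations it gives for claims data are the reporting delay of about nine months and the short window that follows from it. Programme cost is not mentioned.

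At stake is a Bonferroni-tested result for a stated purpose of the trial. A programme that is cost-neutral or more expensive in total could appear cheaper on claims.

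**Working it through.** **No figure to reproduce.** The article states no programme cost, cost standard deviation, expected cost difference or power for this endpoint.

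**Direction.** For each arm, let *C* be the mean claims cost in the six months after initiation and *u* the mean cost of study-supplied components that produce no claim.

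- True difference, intervention minus control: *D* = (*C*_I + *u*_I) − (*C*_C + *u*_C).
- Difference seen in claims: *C*_I − *C*_C = *D* − *c*, where *c* = *u*_I − *u*_C.

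The claims difference is too low by exactly *c*. Because controls have the basic app, *c* is the incremental cost and not the full cost of the intervention. The comparison with the six months before initiation does not remove *c*, since the extra components start only after randomization. If everything is billed, *c* = 0 and there is no bias.

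**Consequence for the test (illustration only).** Inputs:

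- 500 evaluable patients (Sample Size Calculation) at 1:1, so 500/2 = 250 per arm. Claims data for all of them is an assumption.
- Bonferroni level 0.05/8 = 0.00625, assuming that each of the eight secondary rows in Table 1 counts once. The critical value is *z* = 2.734. At an unadjusted 0.05 it is 1.960.
- True total costs equal (*D* = 0).
- *c* expressed as a fraction of the unknown SD of the cost measure.

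The standard error of the difference in SD units is √(2/250) = 0.0894. By normal approximation, P(significant apparent saving) = Φ[(*c*/SD)/0.0894 − *z*]. For *c*/SD = 0.1 at the Bonferroni level: 0.1/0.0894 = 1.118, 1.118 − 2.734 = −1.616, and Φ(−1.616) = 0.053.

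| *c*/SD | level 0.05/8 | level 0.05 |
|---|---|---|
| 0 | 0.003 | 0.025 |
| 0.05 | 0.015 | 0.081 |
| 0.1 | 0.053 | 0.200 |
| 0.2 | 0.309 | 0.609 |
| 0.3 | 0.732 | 0.918 |

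Nothing in the article shows which row applies. Claims come from the participating insurance, so fewer than 500 patients may have them. That would lower these probabilities but leave the bias *c* unchanged. The table applies to a comparison of means. The Brunner-Munzel test, which the plan would use for non-normal costs, would be pushed in the same direction by a different amount.

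**The case against.** The strongest reply is that a claims comparison is a legitimate estimand. Claims can show whether insurer-paid use of care fell without any costing of the programme, and the choice between a payer view and a full costing is partly one of perspective. The article calls cost saving an aim and does not make the claims test the rule for declaring it met. The article also condenses a fuller protocol, and a health-economic plan that is not shown may add programme costs.

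Much of this stands. It limits the point to the endpoint's label, its single stated source and the conclusion drawn from it. It does not remove the point, because Table 1 positively fixes claims as the only source for a cost described as overall, and the article places that endpoint beside a cost-saving aim.

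Three stronger readings are tempting, and the article supports none of them.

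- A reader might infer that claims definitely omit SMARTGEM's cost. The article is silent on funding and billing, so the omission is a condition and not a fact.
- A reader might infer that the chat replaces billed visits, so that savings are counted while spending is left out. The Discussion says only that patients can reach an expert without coming into the office and that access may become easier. It does not say that visits are replaced.
- A reader might want a euro amount per patient. Slot number, slot length and hourly rate would all have to be invented. Spreading the whole operating period over the intervention arm would also be wrong, since the endpoint covers six months and former controls could use the same services after month 6.

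**Conclusion.** The point holds in conditional form. As written, the endpoint measures insurer-paid cost. It cannot support a conclusion about overall cost or cost saving unless SMARTGEM's components are in the claims or their cost is added. If they are unbilled, the error favours the intervention by the mean incremental cost per patient over six months. It is zero if they are fully billed or costed elsewhere. Its size in money is unknown. On the assumptions above, an unrecorded cost of 0.05 SD or less does little harm to the adjusted test, while 0.2 SD or more would often produce a false saving.

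The primary outcome is unaffected. The change is still worth making, because cost reduction is a stated purpose of the trial and the remedy is small.

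**What to change.** State which components (full app, platform, physician time for chat, forum and telemedicine) already appear in the claims. For those that do not, add their incremental six-month cost to the intervention arm: full app over basic app, platform operation, and physician hours at a rate fixed in advance. Charge only the share of platform and physician time that falls in the six-month window and serves intervention patients, and state the allocation rule, since trial-capacity slots spread over few patients may not reflect routine cost. Make this total the tested endpoint, show the claims-only difference beside it, and base any cost-saving conclusion on the total.

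If the costing is not done, relabel the endpoint in Table 1 as insurer-paid costs excluding the intervention, draw no cost-saving conclusion from it, and add the omission to the claims-data limitations in the Discussion.

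The cost is a small costing exercise (app price, platform expense, physician hours) with no new patient data, and probably a less favourable cost result. Relabelling alone costs only wording.
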